## **9 Criteria for Response, Progression, and Relapse**

### **9.1 Definitions**

See clinical section 9.4

### **9.2 Guidelines for evaluation**

Not applicable.

### **9.3 Molecular**

**Primary – not applicable.**

**Secondary – not applicable.**

### **9.4 Clinical**

We define disease progression as: PSA doubling time within 3 months; any adverse pathological findings at baseline, three, six, nine, or 12 months if extended pattern biopsies are performed with a Gleason sum  $\geq 7$  (see exception below); involvement of  $> 50\%$  of any core;  $> 1/3$  of cores positive; or other incidental evidence of clinical progression (i.e. positive bone scans or lymph node biopsies). Any patient exhibiting progression at any time will be withdrawn from the study and offered standard treatment options. Any patient may also withdraw from the protocol at any time for any reason and be offered standard treatment.

If extended pattern biopsies are performed with a Gleason sum  $\geq 7$ , but with a pattern 4 seen as a microfocus ( $< 2\text{mm}$  in length), this will not exclude the patient from continuing on trial.

Regarding the 4 core research biopsies, if involvement of  $> 50\%$  of any core or  $> 1/3$  of cores are positive, this will NOT exclude the participant from continuing in the study unless a Gleason pattern 4 is seen (if Gleason pattern 4 is seen as a microfocus [ $< 2\text{mm}$  in length] this will not exclude the patient from continuing on trial).

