##### **3.2.2 Secondary efficacy outcome measures**

- 3.2.2.1 The secondary aim of identifying genes correlated with nutritional supplementation with lycopene or fish oil will be accomplished by analyzing gene expression of 30,000 human genes using a cDNA array. Identification of a gene cluster associated with lycopene or fish oil but not placebo will be

accomplished using hierarchical clustering[62], or alternate algorithms that use permutation t-test statistics to account for the multiplicity of tests accomplished using such large scale microarrays[63]. If sufficient nucleic acid samples remain after primary outcome measure assessment, and microarray analysis, confirmatory Taqman quantitative polymerase chain reactions will be used to confirm the specific induction of genes identified in these studies by lycopene or fish oil.

- 3.2.2.2 To accomplish the secondary aim of identifying genes correlated with baseline dietary intake, patients will be stratified for high and low intake of total energy, fat/meat/animal products, dairy/calcium, fish, vegetables, tomatoes/lycopene, vitamin E, and selenium as defined by the Willett Semi-quantitative Food Questionnaire. Separate microarray data analyses will be performed for each dietary factor by placing all patients with low intake ( $\leq$  median) into the first half of the data table, and subsequently all patients with high intake ( $>$  median). The same standard microarray hierarchical clustering and permutation t-test approaches as in 3.2.2.1 will then be used to identify genes whose expression differs between these groups.
- 3.2.2.3 We acknowledge that the study is underpowered to assess effects of nutrition supplementation on progression rates, given the heterogeneous nature of prostate adenocarcinoma. Nevertheless, it is compelling to perform exploratory data analysis to examine whether exploratory analysis may detect genes correlated with progression or lack of progression at 12 months in the MENS study. If any correlates are detected, they will be used to formulate a hypothesis for testing in further large scale studies, such as the multi-institutional CALBG or SWOG watchful waiting trials.
- 3.2.2.4 With watchful waiting, approximately 25% of patients will experience disease progression when assessed 12 months after study entry. To assess whether the

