## **4.2 Eligibility**

### **Inclusion criteria**

- Histologically documented, untreated prostate adenocarcinoma, (small cell acinar type).
- Patients must have had an extended pattern biopsy (defined as 8+ cores) within 2 years of the screening date. Potential subjects who meet all of the eligibility criteria EXCEPT for the aforementioned extended pattern biopsy within two years of the screening date, may enroll in the study if they have an extended pattern clinical biopsy scheduled within 6 weeks of the Intervention start date. They must also be willing to have an additional 4 biopsy cores taken for research at this appointment, as well as have the other baseline data collected (QOL, FFQ, 3-day food diary, blood and urine specimens, and a H and P) prior to this biopsy. If the extended pattern clinical biopsy does not meet the inclusion criteria, they will be dropped from enrollment. Final eligibility will be determined after a review of the extended pattern clinical and research biopsy cores by the UCSF Department of Pathology. The purpose of this is to avoid an additional biopsy. If a patient has had a biopsy outside of UCSF, a UCSF pathologist must review the biopsy slides [UCSF pathology review of the most current biopsy slides that indicate malignancy].
- Patients must have 3 serum PSA levels done at least 2 weeks apart over the past year prior to randomization.
- Patients must have PSA  $\leq 10.0$ , (PSA  $< 15$  will be allowed for trial eligibility for patients with benign prostatic hyperplasia or prostatitis), Gleason sum  $\leq 6$  with no pattern 4 or 5 histology (if Gleason pattern 4 is seen as a microfocus [ $< 2\text{mm}$  in length])

this will not exclude the patient from trial eligibility), and clinical stage T1 or T2a.

Patients must have no more than 33% of biopsy cores positive (if  $\geq 33\%$  of biopsy cores are positive due to microfoci of adenocarcinoma, this will not exclude the patient from trial eligibility), and no more than 50% of the length of a tumor core involved by carcinoma. These criteria are based on the literature in watchful waiting[59, 60], and are expected to minimize the risk that a patient would develop metastatic disease as a result of participating in the study.

- Life expectancy of greater than 3 months and ECOG performance status  $\leq 2$  are required
- Ability to understand and willingness to sign an informed consent document.

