bpatients who have donated prostate needle biopsy tissue within 3 months of study entry to the existing Prostate Cancer Tissue Bank will not undergo the initial TRUS biopsy, since their gene expression pattern will have already been comprehensively assessed, and RNA for the primary study aims banked.

cneed for the 12 month TRUS biopsy will be determined by the PSA progression criteria in section 9.4. Some patients, specifically those whose PSA doubling time remains > 12 months at the final study visit will not be asked to undergo the 12 month biopsy.

d three serum PSAs at least 2 weeks apart over the past year to permit calculation of a PSA doubling time [77] must be available. For those patients without serial PSA measurements, randomization will be delayed until collection of the third PSA. Patients with PSA doubling time < 3 months are ineligible to participate.

ePatients will remain on the assigned intervention – placebo, lycopene or fish oil, until the follow-up appointment for transrectal ultrasound and prostate biopsy occurs. Due to scheduling constraints, such as the occurrence of weekends or holidays, it is anticipated that some patients may have to stay on supplement between one to two weeks longer than the literal three month period. Any patient where repeat biopsy cannot be obtained by 14 weeks after beginning intervention will be censored.

fSerum and urine are banked at study entry but not used in the primary data acquisition. These resources are anticipated for possible future confirmatory studies if predictors of progression are identified. Patients will initial their consent for these samples at the end of the informed consent form.

gThe three month research biopsies will be performed at no cost to the participating study subjects.

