For the secondary specific aims (aims 1.2 through 1.4 defined above), we will consider a microarray dataset with measurements for 30,000 genes. For this exploratory investigation genes will be treated as being independent so as to first identify all possible genes that may indicate an effect due to the nutritional supplement (Aim 1.2) or to other dietary components (each considered as a binomial variable) (Aim 1.3). Fisher's exact test will be used to determine which genes result in differences in proportions with up or down regulated genes between groups. No adjustment for multiple comparisons will be made. Also, after all patients have had the potential to be followed for at least one year, they will be classified as to whether they had experienced disease progression within 1 year from protocol entry. The same exploratory techniques described above first using the baseline gene expression profile will be carried out to identify genes that may be associated with disease progression (Aim 1.4). Even though any nutritional supplement will be stopped at 3 months from the start of protocol therapy and the duration of any effect is unknown, this analysis will be repeated using the 3-month gene expression profile to identify the effects of any gene that might have been modified by protocol treatment. To account for genes with highly variable expression regardless of study arm, genes whose expression levels change two-fold in more than 20% of men on placebo (comparing three-month to baseline) will

be excluded from subsequent consideration. This might exclude possible predictors of outcome, but if there is variability within the placebo group then the results may be biased. This refining process will isolate potential predictors of nutritional change when assessing the primary as well as the secondary outcomes. Standard microarray gene expression software algorithms will facilitate analyses to determine if there are individual genes or clusters of genes associated with either supplement, dietary component or disease progression[62, 63] . Fisher's exact test will be used to determine which genes result in statistically significant differences between the groups.

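### Section 9.4 has no counterpart to the microfocus waiver on core count in 4.2, so a man admitted above one third can be recorded as progressed without any increase

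*Protocol*

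**What the plan says.** **Entry.** Protocol 4.2 (Inclusion criteria) requires an extended-pattern biopsy of at least 8 cores and caps positive cores at 33%. It then waives the cap: if 33% or more "of biopsy cores are positive due to microfoci of adenocarcinoma, this will not exclude the patient from trial eligibility". The waiver has no upper limit. For men whose clinical biopsy is done at enrolment, the same section says "Final eligibility will be determined after a review of the extended pattern clinical and research biopsy cores by the UCSF Department of Pathology".

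**Progression.** Protocol 9.4 lists adverse findings on extended-pattern biopsies at baseline and at 3, 6, 9 and 12 months. Among them is more than 1/3 "of cores positive; or other incidental evidence of clinical progression". The threshold is absolute. The consequence is stated without qualification: "Any patient exhibiting progression at any time will be withdrawn from the study and offered standard treatment options".

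**Exceptions in 9.4.** There are two. One covers a Gleason sum of 7 or more on an extended-pattern biopsy when pattern 4 is only a microfocus. The other covers the four-core research biopsies: if more than half of a core or more than a third of cores is involved, "this will NOT exclude the participant from continuing in the study unless a Gleason pattern 4 is seen".

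**Who is re-biopsied.** Note c to the study table (8.6) makes the 12-month biopsy depend on PSA. Men whose doubling time stays above 12 months "will not be asked to undergo the 12 month biopsy".

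**Where progression is used.** Section 13 closes accrual if six or more of the first ten men on a supplement arm progress by 12 months. For Aim 1.4, "they will be classified as to whether they had experienced disease progression within 1 year from protocol entry". Aim 1.5 is a log-rank comparison of each supplement arm with control.

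**The concern.** Section 4.2 has two microfocus waivers, one for pattern 4 and one for core count. Section 9.4 repeats the first and omits the second. The core count that 4.2 accepts at entry is thus, on the same kind of biopsy, a reason for withdrawal under 9.4. Because 9.4 does not refer back to the entry biopsy, it cannot separate a man who has worsened from one who was already above one third when admitted.

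For the man himself, the result is removal from the study and an offer of treatment for a finding that the protocol had accepted. For the trial, such an event matters most in the interim rule. That rule is a raw count within one arm of ten, set against a 25% background rate, with no comparison with placebo to cancel errors common to all arms. In Aims 1.4 and 1.5 the misclassification should fall about equally across randomised arms and mainly adds noise.

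**Working it through.** **1. Does either exception in 9.4 reach the case?** The case is an extended-pattern biopsy with more than a third of cores positive, through microfoci only, without pattern 4 and with no core more than half involved.

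| Provision | Biopsy it applies to | What it excuses | Covers the case? |
|---|---|---|---|
| 4.2 waiver | entry | 33% or more positive through microfoci | at entry only |
| 9.4, first exception | extended pattern | pattern 4 as a microfocus | no (wrong criterion) |
| 9.4, second exception | four research cores | more than 1/3 positive, or more than 50% of a core | no (wrong biopsy) |

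Neither does.

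**2. Where the conflict starts.** The waiver applies from 33% upward; progression needs strictly more than 1/3. The smallest counts above one third are 3/8 = 37.5%, 4/10 = 40%, 5/12 = 41.7% and 5/14 = 35.7%. A man at 4/12 = 33.3% needs the waiver but does not meet the 9.4 criterion, so he is not affected.

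**3. When it can happen.**
- Baseline: 9.4 names baseline among its time points. Read literally, a waiver man meets the criterion on his entry biopsy. The sensible reading is that 4.2 governs entry slides, but 9.4 does not say so.
- 3 months: four research cores, exempt.
- 12 months: extended-pattern biopsy, but PSA-driven. The only PSA criterion in 9.4 is a doubling time within 3 months, and a man who meets it has progressed already. The core count therefore adds events mainly among men with doubling times of roughly 3 to 12 months, and in any man biopsied outside the schedule.

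**4. The protocol's own interim figure.** Section 13 gives a 95% lower bound of 30.4% at the stopping boundary. The exact one-sided lower bound for 6/10 is the 5% quantile of Beta(6, 5) = 0.3035, which agrees. At the assumed 25% rate, P(Bin(10, 0.25) ≥ 6) = 0.0197, or 2.0% per arm.

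**5. Effect on the false-stop chance.** The protocol gives neither the number of waiver men nor their re-biopsy rate, so these inputs are assumptions:
- k = waiver men among the ten: 1 or 2.
- q = share of them re-biopsied and still above one third through microfoci: 10% to 50%.
- pt = share of those men who have truly progressed: 0.50, because re-biopsy is triggered by PSA. With true progression at 25% overall, q × pt cannot exceed 0.25, so q cannot exceed 0.50.

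Event probability for a waiver man: pe = 0.25 + q(1 − pt). Stop probability: P = Σⱼ Bin(j; k, pe) × P(Bin(10 − k, 0.25) ≥ 6 − j).

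Tail values: for 9 men, P(≥5) = 0.0489 and P(≥6) = 0.0100. For 8 men, P(≥4) = 0.1138, P(≥5) = 0.0273 and P(≥6) = 0.0042.

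| q | pe | k = 1 | k = 2 |
|---|---|---|---|
| 0.10 | 0.300 | 2.17% | 2.38% |
| 0.25 | 0.375 | 2.46% | 3.05% |
| 0.50 | 0.500 | 2.95% | 4.32% |

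Example, k = 1, q = 0.50: 0.5 × 0.0489 + 0.5 × 0.0100 = 0.0295.

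Example, k = 2, q = 0.50: 0.25 × 0.1138 + 0.50 × 0.0273 + 0.25 × 0.0042 = 0.0432.

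**The case against.** The best defence is that the two sections serve different ends. Section 4.2 decides who may enter; 9.4 decides when a man should leave and be offered treatment. A stricter, absolute threshold on a biopsy prompted by PSA is a defensible safety choice in a protocol that stresses curative intent. A man with a shortening doubling time and more than a third of cores positive is also not plainly stable. Finally, microfoci would have to be hit again in at least 3 of 8 or 5 of 12 cores, and nothing in the protocol says how often that happens.

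Much of this stands. It limits the number of men affected, and it means that any exemption must not hide a real rise in positive cores. It does not justify an absolute threshold for men admitted above it. Without a comparison with entry, the criterion gives the same answer whether or not anything has changed, and the protocol offers no reason for carrying over one microfocus waiver and not the other.

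A reader might infer larger numbers. If re-biopsy were independent of progression (pt = 0.25), the same formula gives 2.3%–3.4% with one waiver man and 2.6%–5.8% with two. If every waiver man were re-biopsied and still above one third, it gives 4.9% and 11.4%. Note c does not support these: the 12-month biopsy follows PSA and is not asked of men with long doubling times.

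**Conclusion.** The omission is certain from the text; its size is not. A waiver man above one third at entry, with no increase on an extended-pattern biopsy, is recorded as progressed and withdrawn, and he counts toward the interim rule and in Aims 1.4 and 1.5. Under the assumptions that fit a PSA-driven re-biopsy, the false-stop chance per arm moves from 2.0% to 2.2%–2.9% with one such man among ten and to 2.4%–4.3% with two. The number of waiver men, their re-biopsy rate and the share truly progressed are all assumed.

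Two further inferences should be resisted. The primary endpoint is not materially threatened: its tissue is taken at 3 months, those research cores are exempt, and the 12-month biopsy comes about nine months later. The progression comparison is not undone either, since the protocol says of it: "We acknowledge that the study is underpowered to assess effects of nutrition supplementation on progression rates". This is a minor point, worth correcting because 9.4 as written gives a wrong result for these men and the repair is small.

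**What to change.** Add to 9.4:

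1. The core-count criterion does not apply to the biopsy used to establish eligibility.
2. For men admitted under the microfocus exception in 4.2, more than one third of extended-pattern cores positive through microfoci alone is not progression unless the proportion positive exceeds that at entry.

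Keep the Gleason, more-than-50%-of-core, PSA and clinical criteria for all men, and the one-third rule for everyone not admitted under the waiver. The comparison with entry is what answers the safety objection, because a real rise in the proportion of positive cores still triggers withdrawal.

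The cost is two sentences, with no new data or procedures beyond using the entry core count, which eligibility review already requires. The downside is a slightly less strict core-count trigger for the few waiver men.

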## **10 Safety and ethical considerations**

### **10.1 Safety plan – Oversight and Monitoring**

The UCSF Comprehensive Cancer Center (UCSFCCC) Data Monitoring Committee (DMC) is responsible for monitoring data quality and patient safety for all UCSFCCC clinical studies. Phase I-III nutrition trials are required to have a data safety and monitoring plan commensurate with patient risk approved by the protocol review committee (PRC). A summary of DMC activities follows:

- Review of all clinical trials conducted at the UCSFCCC for progress and safety
- Review of all adverse events requiring expedited reporting as defined in this protocol
- Review of reports generated by the UCSFCCC data quality control review process
- Submit recommendations for corrective action to the Clinical Research Steering Committee (CRSC)
- Notify the Principal Investigator of the DMC recommendation to the CRSC
- Notify external sites

### **10.2 Assessment of safety**

#### **Assessment of Safety**

Toxicity is not expected in the MENS study, and since there is a stopping rule for efficacy, no patient should be harmed by participation in this protocol. Many of the past studies of omega-3 supplementation in humans studied coronary atherosclerosis using angiography. Despite cannulation of the arterial system after more than two years of 12-gram per day supplementation, no bleeding complications occurred in this study[70]. Likewise, there are no - expected side effects from lycopene supplementation[41].

Serum PSA and clinical progression will be monitored at visits approximately every three months.

## Adverse Events

### 10.2.2.1 Adverse Event Reporting (AER)

#### 10.2.2.2 Investigational Drug Branch (IDB)

Investigators are required by Federal Regulations to report serious adverse events as defined in the table below. Investigators are required to notify the Investigational Drug Branch (IDB), Principal Investigator and their Institutional Review Board if a patient has a reportable serious adverse event (follow guidelines in the table below). This study will utilize the Common Toxicity Criteria version 2 to determine the severity of the reaction for adverse event reporting.

Investigators are also required to report secondary malignancies occurring on or following treatment on NCI-sponsored protocols. Reporting of cases of secondary AML/MDS is to be performed using the NCI/CTEP Secondary AML/MDS Report Form. This form should be used in place of the form FDA #3500 (Medwatch). All other secondary malignancies should be reported using the form FDA #3500 (Medwatch).

### 10.2.2.3 Expedited reporting for adverse events (including hospitalization defined below) attributable to investigational agent(s) is required as in Table 1

**TABLE 1: Expedited Reporting for Phase 2 and Phase 3 Studies**

| UNEXPECTED EVENT                                                         |                                                 | EXPECTED EVENT |                                                 |
|--------------------------------------------------------------------------|-------------------------------------------------|----------------|-------------------------------------------------|
| GRADES 2 – 3

Attribution of Possible,

Probable or Definite | GRADES 4 and 5

Regardless of Attribution | GRADES 1 – 3   | GRADES 4 and 5

Regardless of Attribution |

|                                                                                                                  |                                                                                                                                                                                                                                                                                                                                                                  |                                                        |                                                                                                                                                                                                                                                                                                                                                                                                                                                                                                      |
|------------------------------------------------------------------------------------------------------------------|------------------------------------------------------------------------------------------------------------------------------------------------------------------------------------------------------------------------------------------------------------------------------------------------------------------------------------------------------------------|--------------------------------------------------------|------------------------------------------------------------------------------------------------------------------------------------------------------------------------------------------------------------------------------------------------------------------------------------------------------------------------------------------------------------------------------------------------------------------------------------------------------------------------------------------------------|
| 
Expedited report within 10 working days.
 
(Grade 1 Adverse Event Expedited Reporting NOT required.)
 | 
Report by phone to IDB within 24 hrs. Expedited report to follow within 10 working days.
 
This includes all deaths within 30 days of the last dose of treatment with an investigational agent regardless of attribution.
 
Any late death attributed to the agent (possible, probable, or definite) should be reported within 10 working days.
 | 
Adverse Event Expedited Reporting NOT required.
 | 
Expedited report, including Grade 5 Aplasia in leukemia patients, within 10 working days.
 
This includes all deaths within 30 days of the last dose of treatment with an investigational agent regardless of attribution.
 
Any late death attributed to the agent (possible, probable, or definite) should be reported within 10 working days.
 
Grade 4 Myelosuppression or other Grade 4 events that do not require expedited reporting will be specified in the protocol.
 |
|------------------------------------------------------------------------------------------------------------------|------------------------------------------------------------------------------------------------------------------------------------------------------------------------------------------------------------------------------------------------------------------------------------------------------------------------------------------------------------------|--------------------------------------------------------|------------------------------------------------------------------------------------------------------------------------------------------------------------------------------------------------------------------------------------------------------------------------------------------------------------------------------------------------------------------------------------------------------------------------------------------------------------------------------------------------------|

- For **Hospitalization** only - Any medical event equivalent to CTC Grade 3, 4, 5 which precipitated hospitalization (or prolongation of existing hospitalization) must be reported regardless of expected or unexpected and attribution.
- Telephone reports to the Investigational Drug Branch at [contact] available 24 hours daily (recorder between 5 pm and 9 am EST).
- Expedited reports are to be submitted using AdEERS or the paper templates available at <http://ctep.cancer.gov/> The NCI Guidelines for expedited adverse event reporting are also available at this site.
- A list of agent specific expected adverse events can be found in the Appendix A-1.
- Includes reporting of all deaths within 30 days of the last dose of treatment regardless of attribution.

